According to the results of our previous observational study involving Mokhuri nonsurgical integrative treatments performed on patients diagnosed with Meyerding grade 2 lumbar spinal spondylolisthesis, considerable clinical improvement was observed after nonsurgical integrative treatments; the average walking distance without pain increased from 55 to 165 m, while the intensity of pain experienced when walking was reduced by 80% compared with the baseline assessment.^[7]^ In another previous retrospective audit study, on a numeric rating scale from 0 to 10, 44 spondylolisthesis patients reported a reduction in numeric rating scale scores from 7.1 to 3.1, and walking distance without pain increased from 193 to 568 m after treatment.^[8]^ These observational studies provide clues for the potential benefit of nonsurgical integrative treatments and suggest that these treatments might be effective for pain relief and functional restoration in patients with symptomatic lumbar spinal spondylolisthesis. However, observation studies cannot provide clinical evidence, so these new therapeutic options should be evaluated through rigorous, high-powered clinical trials.

The objective of this study is to assess the effectiveness and the safety of a 5-week Mokhuri treatment program compared with conventional nonsurgical treatments for symptomatic lumbar spondylolisthesis.

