### Study design

2.1

This is a study protocol for a multinational, multicenter clinical randomized controlled trial that is designed to evaluate the effectiveness and safety of nonsurgical integrative treatment in patients with symptomatic lumbar spinal spondylolisthesis who continue to have symptoms after a sufficient duration of conservative treatment. Patients with symptomatic lumbar spinal spondylolisthesis will be randomly allocated to one of the interventions: a 5-week Mokhuri treatment program (Chuna, acupuncture, and patient education) or nonsurgical conventional standard treatment (drugs for pain relief, epidural steroid injections, and physical therapy). The trial participants who agree to participate in the clinical trial after written informed consent will undergo the required examinations and tests according to the plan for the clinical trial. After 5 weeks of treatment, the clinical outcomes of both groups will be evaluated during follow-up, which will take place at 7, 18, 30, 54, and 102 weeks after the end of the treatments.

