### Interventions

2.4

All the participants in each group will undergo 5 weeks of treatments. In the Mokhuri treatment group, participants will undergo 10 sessions of acupuncture therapy, Chuna therapy, and consultation with physicians. In the control group, participants will be administered drugs every day, have 1 or 2 epidural steroid injections, and participate in 10 sessions of physical therapy for 5 weeks.

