### Outcomes

2.10

The validated English version for the Mayo Clinic and the Korean version for the Mokhuri hospital will be used for all the outcome assessments. Outcome assessors will be blinded to the allocation results.

The primary outcome will be VAS scores from 0 to 100 for low back pain. The degree of pain will be evaluated on a 100 mm straight line, where the left edge of the straight line will indicate “0: no symptoms,” and the right edge will indicate “100: the most severe pain.” The participant will indicate the average level of lumbar pain experienced for the past week.

The secondary outcomes will include VAS scores from 0 to 100 for leg pain, EQ-5D scores, Oswestry disability index (ODI) scores, Roland–Morris Disability Questionnaire (RMDQ) scores, Zurich Claudication Questionnaire (ZCQ) scores, walking duration and distance without leg pain, a 5-minute treadmill test, the ratio between the actual duration of participation and the originally scheduled duration in each group, the presence of any additional spondylolisthesis treatments, the types of concomitant treatments during the follow-up period, and adverse events (AEs).

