
### Participant time schedule

2.11

At the screening visit, participants will be given detailed explanations of the objectives and contents of this clinical trial and will receive the written agreement form. During this visit, a 5-minute treadmill test, lumbar physical and radiological examinations, ankle-brachial index assessment (or Doppler ultrasonography of lower limbs if necessary), bone mineral densitometer assessment, and inclusion criteria assessment will be conducted. If the participant can be enrolled in the study, random assignment of the participant will take place at the following visit. Before the treatments begin, the VAS scores for low back pain and for leg pain, EQ-5D scores, ODI scores, RMDQ scores, ZCQ scores, walking duration and distance free of leg pain, and a treadmill test will be assessed. After that, participants will undergo 10 treatments over 5 weeks. After treatment, evaluations will be performed immediately (7 weeks) and at 18 weeks, 30 weeks, 54 weeks (1-year follow-up), and 102 weeks (2-year follow-up). AEs will be assessed at each visit (Table 1).

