### Sample size

2.12

To calculate the sample size, a retrospective study performed on 44 patients with lumbar spinal spondylolisthesis^[8]^ and the previous clinical trial data that assessed physical therapy for hospitalized patients in a similar study setting^[18]^ were used. To determine a meaningful difference between groups, a minimal clinically important difference of 2.5 points on the numeric rating scale of 0 to 10 was used.^[19]^ The standard deviation (SD) was 4.65 from the abovementioned previous studies. For the sample size calculation, the significance level (α) was 0.05, and the power (1–β) was 0.80. The following formula was used for the calculation. Assuming a drop-out rate of 10%, 61 participants will be needed in each study group, yielding a total of 122 participants needed for this study. 
[figure not shown]

In terms of the total 122 participants in the study, 108 participants will be recruited at the Mokhuri Oriental Medicine Hospital and 14 participants at the Mayo Clinic.

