### Statistical analysis

2.13

Statistical analysis will be performed based on an intention-to-treat analysis for the assessment of effectiveness outcomes and a per-protocol analysis for the assessment of safety. The missing values will be substituted with the most recently observed value (the last observation carried forward method). For the demographic information, continuous data will be presented as the mean and SD, and categorical data will be reported with a frequency table. The 2-sample *t* test (or Wilcoxon rank-sum test) will be used for the analysis of continuous variables after evaluating the data distribution. For categorical data, the chi-square test (or Fisher exact test) will be used. Outcome variables including VAS scores for lumbar pain and leg pain, EQ-5D scores, ODI scores, RMDQ scores, ZCQ scores, walking duration and distance without leg pain, and the treadmill test will be summarized with means and SDs. For statistical analysis of continuous outcomes, changes in the scores before and after treatments will be regarded as dependent variables, with the baseline scores and research institutions as covariates and the groups as fixed factors, to perform the analysis of covariance. To verify the trends for each visit in the 2 groups, repeated measures analysis of variance will be performed. For categorical outcome data, the chi-square test (or Fisher exact test) will be used.

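### Last observation carried forward as the stated method for all missing values can bias the 1- and 2-year pain comparisons in either direction and usually overstates their precision

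*Protocol article*

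**What the plan says.** The Statistical analysis section (2.13) of the protocol article fixes the rule: "The missing values will be substituted with the most recently observed value (the last observation carried forward method". It covers every missing value and is the only missing-data method named. The effectiveness analysis is by intention to treat. It uses ANCOVA on change, adjusted for baseline score and institution, and adds: "To verify the trends for each visit in the 2 groups, repeated measures analysis of variance will be performed".

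The setting matters for judging this rule:
- Interventions (2.4): "All the participants in each group will undergo 5 weeks of treatments".
- Study design (2.1) places the visits as follows: "which will take place at 7, 18, 30, 54, and 102 weeks after the end of the treatments". Participant time schedule (2.11) treats week 7 as the visit straight after treatment: "evaluations will be performed immediately (7 weeks) and at 18 weeks, 30 weeks, 54 weeks (1-year follow-up), and 102 weeks (2-year follow-up".
- Outcomes (2.10): "The primary outcome will be VAS scores from 0 to 100 for low back pain". No primary time point is given there or in 2.13. The same section lets participants use other treatments for their condition once the study treatment has ended.
- Sample size (2.12) allows for 10% drop-out and arrives at 61 per group.

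**The concern.** Carrying a value forward assumes that pain stays where it was when the person was last seen. In this trial a week-7 score may be copied to week 102, a gap of 102 - 7 = 95 weeks with no study treatment and with other treatments permitted. The article gives no argument that pain is stable over that time. Its Introduction reports large movement in an earlier audit, where "44 spondylolisthesis patients reported a reduction in numeric rating scale scores from 7.1 to 3.1".

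Two things are at stake. First, if the arms lose people at different rates or times, or their pain follows different courses, the copied values shift the difference between groups. Second, copied values are analysed as if observed. That overstates the information at late visits and adds flat stretches to the within-person profiles used by the repeated measures ANOVA. The 1- and 2-year comparisons are the most exposed.

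**Working it through.** **1. The plan's own figure.** Inputs from Sample size: difference 2.5 on a 0-10 scale, SD 4.65, alpha 0.05 (two-sided reproduces the result), power 0.80. n = 2 x (1.960 + 0.842)² x 4.65² / 2.5² = 2 x 7.849 x 21.62 / 6.25 = 54.3 per group; 54.3 / 0.9 = 60.3, rounded up to 61. The stated size reproduces. It counts drop-outs as contributing nothing: 0.9 x 122 = 109.8 evaluable.

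**2. Bias by hand, drop-out at random.** In one arm, the bias at week 102 is the sum over visits k of P(last seen at k) x (mean at k - mean at week 102). Assume a constant drop-out probability h before each of the five visits. Then P = h(1 - h)^k with k = 0 for baseline, and h = 1 - (1 - d)^(1/5), which is 0.0209 for d = 10% and 0.0689 for d = 30%. The means below are assumptions on the 0-10 scale, for baseline and the five visits.
- *Early benefit that wanes.* Mokhuri 7, 3, 3.6, 4.2, 4.8, 5.5; control 7, then 5.5 throughout; true week-102 difference 0. The baseline terms cancel. At 10%: -0.0209 x (0.979 x 2.5 + 0.959 x 1.9 + 0.939 x 1.3 + 0.919 x 0.7) = -0.0209 x 6.13 = -0.13. At 30%: -0.0689 x 5.55 = -0.38. Both falsely favour Mokhuri.
- *Same improvement, unequal drop-out.* Both arms 7, 5.5, 5, 4.5, 4, 3.5. The 10% arm is off by 0.0209 x 8.29 = 0.17 and the 30% arm by 0.0689 x 7.85 = 0.54, a false difference of 0.37 against the arm with more losses. Swapping the arms reverses the sign.
- *Constant true difference of 2.5* (7 to 3 versus 7 to 5.5). The bias towards zero is h x (4 - 1.5) = 0.05 at 10% and 0.17 at 30%.
- *Equal drop-out and identical trajectories.* The bias is 0.

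**3. Simulation.** 61 per arm, the same means, ANCOVA at week 102. Further assumptions: SD 2.5, correlation 0.6 between adjacent visits and lower further apart. Drop-out was either random or more likely with more pain at the last visit.

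| Scenario (true difference) | Nominal drop-out | LOCF, random | LOCF, pain-dependent |
|---|---|---|---|
| Waning (0) | 10% / 10% | -0.12 | -0.20 |
| | 30% / 30% | -0.41 | -0.48 |
| | 10% / 30% | -0.21 | -0.52 |
| Equal improvement (0) | 10% / 10% | -0.03 | -0.02 |
| | 10% / 30% | -0.39 | -0.67 |
| Constant (-2.5) | 10% / 10% | -2.43 | -2.42 |
| | 30% / 30% | -2.33 | -2.26 |
| | 10% / 30% | -2.50 | -2.77 |

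A likelihood estimate assuming data missing at random stayed within about 0.03 of the truth in every scenario; all scenarios met that assumption. In the pain-dependent runs the realised drop-out exceeded the nominal rate: about 15% for 10% and about 37% for 30%. The upper ends of the ranges belong to those realised rates.

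**4. Precision.** If carried values held no information, the ratio of standard errors would be √(109.8 / 122) = 0.949, about 5% too small. The simulated ratio at 10% random drop-out with a constant difference is 0.433 / 0.454 = 0.954. Across all scenarios it ran from 0.86 to 1.04. The within-patient mean square in the repeated measures ANOVA fell to 0.90-0.95 of its full-data value at 10%, and to 0.74-0.83 at 30%.

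**5. Scale.** Multiply by 10 for the 0-100 VAS. Against the planned difference, 0.20 / 2.5 = 8% and 0.67 / 2.5 = 27%.

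**The case against.** The strongest reply is that little happens at the planned drop-out. A bias of 0.2 is small against 2.5. With the plan's SD of 4.65, the unadjusted standard error is 4.65 x √(2/61) = 0.84, so 0.2 is 0.24 standard errors and lifts the false-positive rate from 5% only to about 5.7%. Baseline adjustment would shrink the standard error and raise that somewhat. This stands, and it limits the severity. The larger effects need about three times the planned drop-out in at least one arm.

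Second, the ANCOVA speaks of change before and after treatment, which may mean week 7, where fewest values are carried. In the waning scenario at 10%, the week-7 bias is only 0.0209 x (4 - 1.5) = 0.05. The repeated measures ANOVA is there to examine trends. That is a fair reading, but no primary time point is stated, and visits run to week 102.

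Third, a statistical analysis plan that is not shown may hold sensitivity analyses. So their absence here is no fault, but such analyses would not change the main method stated in the article.

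A reader might also infer more than the documents support:
- *That a carried value is wrong by up to 40 points, and an arm mean by up to 4.* The 40 is a mean before-after change in 44 treated patients, (7.1 - 3.1) x 10. It does not bound an individual error.
- *That anyone leaving before the first follow-up has baseline carried.* Outcomes describes weekly pain scores during treatment, so a mid-treatment leaver may carry an on-treatment score. Section 2 of the working assumes baseline. The constant-difference bias there comes wholly from that assumption and would change without it.
- *That the condition relapses, that the end-of-treatment score is the best one, or that reasons for leaving differ by arm.* The article calls the condition chronic and says none of these.

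**Conclusion.** The concern holds as a possible bias, not a certain one. Carrying values forward is a poor main method here because its assumption of constant pain has no support in a design with 5 weeks of treatment, follow-up to week 102 and other treatments allowed meanwhile.

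- **Bias, 0-100 scale.** About 0 to 2 points near the planned 10% drop-out (0 to 1.3 by hand at exactly 10% random loss), and up to about 5 to 7 points with drop-out around 30% or unequal at 10% versus 30%. The direction can favour either arm. It would be wrong to read this as a sure advantage for Mokhuri.
- **Timing.** As a rule the effect is least at week 7 and greatest at weeks 54 and 102, because more values are carried over longer gaps. The constant-difference scenario is an exception: by hand the bias there is the same at every visit.
- **Precision.** Standard errors are usually too small for the information available, by about 5% at 10% drop-out. They are not always too small, since the ratio reached 1.04. The ANCOVA standard error does match the sampling spread of the carried-forward estimate itself. Within-patient variation in the repeated measures ANOVA is understated.

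The sizes rest on assumed trajectories, SD, correlation and drop-out patterns. This should be fixed at the planned drop-out, and becomes more serious if 2-year attrition is higher or unequal.

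**What to change.** Replace last observation carried forward as the main method, before any outcome data are seen by arm. Either of two routes answers the point:
- A likelihood-based mixed model for repeated measures on all observed visits, with arm, visit, arm-by-visit, baseline VAS and institution, reading the adjusted difference at each visit. This also takes the place of the repeated measures ANOVA.
- Multiple imputation feeding the planned ANCOVA.

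Keep last observation carried forward at most as a sensitivity analysis. A delta-adjusted analysis is desirable, because both routes assume data missing at random.

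The cost is a change of wording, a little programming and possibly slightly wider confidence intervals. No new data are needed, and the size stays at 122 because 10% drop-out is already allowed for.

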### Inclusion and exclusion criteria

2.3

Individuals who meet all the following criteria will be included as appropriate participants in the clinical trial:(1)Those aged from 19 to 78 years;(2)Those with a diagnosis of degenerative lumbar spinal spondylolisthesis or who have low back pain, lower limb radiating pain, or leg discomfort when standing or walking with a severity of at least 5 on a visual analogue scale (VAS) of 0 to 100 for each symptom;(3)Those suffering from neurologic claudication or radicular pain for at least 1 year;(4)Those with neurogenic claudication within 5 minutes of walking on a treadmill at a speed of 1.5 miles per hour;(5)Those who have not received an epidural injection within the past month;(6)Those who have not undergone lumbar surgery;(7)Those who have confirmed spondylolisthesis on lumbar spine AP, lateral, nd both oblique views;(8)Those who weigh 250 lbs (113.398 kg) or less;(9)Those whose height is 2.1 m (6.890 ft) or shorter; and(10)Those who agreeing to participate in this clinical trial after receiving a thorough explanation of the purposes and characteristics of the trial and who are willing to sign the written informed consent form.

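### The treadmill test is taken twice before treatment, but the treadmill ANCOVA names only the baseline score, so a screening reading that could add some precision goes unused

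*Protocol article*

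**What the plan says.** Section 2.13 (Statistical analysis) fixes the model for all continuous outcomes, including the treadmill test. The change from before to after treatment is analysed by ANCOVA, "with the baseline scores and research institutions as covariates and the groups as fixed factors". Baseline is not defined further.

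Section 2.11 (Participant time schedule) lists the treadmill test at two points. For screening it says: "During this visit, a 5-minute treadmill test, lumbar physical and radiological examinations". Random assignment follows at the next visit. In the assessments made before treatment starts, the list ends with "walking duration and distance free of leg pain, and a treadmill test will be assessed".

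Two other sections bear on the size of the gain. Inclusion criterion 4 (Section 2.3) requires claudication within 5 minutes on a treadmill at 1.5 miles per hour, so the screening test also decides entry. Section 2.10 (Outcomes) makes low back pain VAS the primary outcome and the treadmill test secondary. It defines the treadmill measure as the time until leg pain starts.

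**The concern.** A single walking time is a noisy measure of a person's usual capacity. Two readings describe it better than one, and a better description of the starting point leaves less unexplained variation at follow-up. The screening reading is fixed before randomisation, so adjusting for it cannot bias the treatment comparison.

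As written, the model uses one treadmill value per person and leaves the other out. It also leaves open which value counts as baseline, and that value enters both the change score and the covariate. At stake is a modest amount of precision on a secondary outcome, and a choice that is better fixed in advance.

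**Working it through.** **1. The plan's own figure.** Section 2.12 gives these inputs: "a minimal clinically important difference of 2.5 points on the numeric rating scale of 0 to 10 was used"; "The standard deviation (SD) was 4.65 from the abovementioned previous studies"; "the significance level (α) was 0.05, and the power (1–β) was 0.80". With a two-sided test,

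n per group = 2 × [4.65 × (1.960 + 0.842) / 2.5]² = 54.31.

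Dividing by 0.9 for drop-out gives 60.34, which rounds up to 61. This agrees with the stated result: "Assuming a drop-out rate of 10%, 61 participants will be needed in each study group, yielding a total of 122 participants". The formula is unadjusted and concerns pain, so the planned size takes no credit for any baseline covariate. No SD is given for the treadmill test, so power for that outcome cannot be computed.

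**2. One reading against two, before allowing for selection.** Let r be the correlation of each pre-treatment reading with follow-up, and b the correlation between the two readings. Neither is in the document; both are assumed. Because baseline is in the model, analysing change or the follow-up value gives the same treatment effect and residual variance. In units of the follow-up variance:

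- one reading: V1 = 1 − r²
- two readings: V2 = 1 − 2r²/(1 + b)

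At r = b = 0.5 these are 0.750 and 0.667, a fall of 11%. At r = b = 0.7 they are 0.510 and 0.424, a fall of 17%.

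**3. Allowing for the entry rule.** Criterion 4 admits only people with short screening times, which narrows the range of that reading. Assume normal readings and entry only if the screening value is below c (in SD units). Its variance falls to k = 1 − cλ − λ², with λ = φ(c)/Φ(c). This gives k = 0.630 for a cut at +1 SD and 0.363 for a cut at the mean. After selection:

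- Var(follow-up) = 1 − (1 − k)r²
- Var(baseline) = 1 − (1 − k)b²
- Cov(baseline, follow-up) = r − (1 − k)br
- V1 = Var(follow-up) − Cov²/Var(baseline)
- V2 is unchanged, because it is already conditional on the screening value.

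Example with r = 0.5, b = 0.7, c = +1: Var(follow-up) = 0.9075, Var(baseline) = 0.8187, Cov = 0.3705. Then V1 = 0.9075 − 0.1373/0.8187 = 0.740 and V2 = 1 − 0.5/1.7 = 0.706, a fall of 4.6%.

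Fall in residual variance from adding the screening reading:

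| r | b | no selection | cut at +1 SD | cut at mean |
|---|---|---|---|---|
| 0.3 | 0.3 | 5.3% | 3.5% | 2.1% |
| 0.3 | 0.8 | 1.1% | 0.9% | 0.7% |
| 0.5 | 0.5 | 11.1% | 8.0% | 5.1% |
| 0.5 | 0.7 | 5.9% | 4.6% | 3.2% |
| 0.5 | 0.8 | 3.7% | 3.1% | 2.3% |
| 0.7 | 0.7 | 17.0% | 13.6% | 9.7% |
| 0.7 | 0.8 | 10.7% | 9.0% | 6.8% |

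The two selection columns run from about 1% to 14%. The standard error falls by 1 − √(1 − fall): about 0.5% for a 1% fall and 7% for a 13.6% fall.

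**4. Cost.** With 122 participants, the model with intercept, group, institution and baseline leaves 118 residual degrees of freedom; the extra covariate leaves 117. Estimating one more coefficient costs roughly 1/117, or 0.9%, of the variance. At the bottom of the table the net gain is therefore about nil; elsewhere it is positive.

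**The case against.** The strongest reply is that this is a preference, not a defect. ANCOVA on one baseline is standard and unbiased, the text does not say that repeat readings are ignored, and a full protocol or analysis plan may define baseline. That stands, and it makes this a suggested improvement rather than an error or a contradiction. Still, the article does name the covariates, and the screening reading is not clearly among them.

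A second reply is that the screening test serves as an entry check, and the text does not say that a time, rather than a pass or fail, is recorded there. This also stands. The gain is available only if the time is kept.

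A third is that adjacent readings probably correlate more with each other than with follow-up at 7 to 102 weeks. This is reasonable and points to the lower rows of the table: at r = 0.5 with b of 0.7 to 0.8, the fall under selection is about 2% to 5%.

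A reader might also infer that the primary low back pain VAS loses precision in the same way, since inclusion criterion 2 mentions symptoms "with a severity of at least 5 on a visual analogue scale (VAS) of 0 to 100 for each symptom". The article does not support this. Section 2.11 names no VAS at screening. Criterion 2 joins the diagnosis and the symptoms by an 'or', so it can be read as met by diagnosis alone. Its symptoms are those felt on standing or walking, while the primary outcome is the past week's average lumbar pain. Recording a screening VAS for everyone would be new data collection, not the use of a value in hand.

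**Conclusion.** The point holds for the secondary treadmill outcome only. Two pre-treatment treadmill tests are documented, the first certainly before randomisation, and the model in Section 2.13 names only the baseline score. Using both would lower residual variance by about 1% to 14%, and the standard error by about 0.5% to 7%. That range assumes follow-up correlations of 0.3 to 0.7, approximately normal readings, and truncation of the screening value at its mean or at +1 SD.

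It would be wrong to infer that the trial is underpowered or its analysis biased. The 61 per group comes from an unadjusted formula, so the stated 80% power does not rely on a second reading, and the single-baseline ANCOVA is valid. The 11% to 17% gains from the simple formula at r = b = 0.5 to 0.7 should not be quoted for this trial either, because they ignore selection and any closer correlation between the two readings. No claim is made for low back or leg pain VAS. This is a low-priority improvement.

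**What to change.** Add one sentence to Section 2.13: for the treadmill outcome, baseline is the reading taken before treatment begins, and the screening treadmill time enters the ANCOVA as a second covariate beside baseline and institution. Confirm that the screening test records the time to leg pain in the same way as the outcome test. The models for the pain VAS and the other outcomes stay as they are.

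The cost is that sentence and one degree of freedom in one secondary analysis. It needs no new visit, no extra test and no change to the sample size.

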### Sequence generation and allocation concealment

2.9

Two sets of random sequences will be generated for the 2 research institutions using the statistical program SAS (SAS institute Inc, Cary, NC) by an independent statistician. The block size will not be known to the investigators so as not to predict the random sequence. All participants will have equal chances of being selected for either the Mokhuri treatment group or the control group. Sealed opaque envelopes with the assigned results for each participant will be used for allocation concealment. The investigators at each of the study institutions will open a random assignment envelope and assign the participant to an intervention group in the consecutive order of the patients’ serial numbers.

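### Categorical outcomes are tested without institution although randomisation is by institution: a minor loss of power, and a possible site imbalance in the safety comparison

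*Protocol article*

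**What the plan says.** Section 2.9 of the protocol article sets up randomisation by site: "Two sets of random sequences will be generated for the 2 research institutions using the statistical program SAS". Allocation is 1:1: "All participants will have equal chances of being selected for either the Mokhuri treatment group or the control group". Section 2.12 gives the planned stratum sizes: "108 participants will be recruited at the Mokhuri Oriental Medicine Hospital and 14 participants at the Mayo Clinic".

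Section 2.13 carries the site into the analysis of continuous outcomes, which is done "with the baseline scores and research institutions as covariates and the groups as fixed factors, to perform the analysis of covariance". This covers the primary outcome, since section 2.10 states: "The primary outcome will be VAS scores from 0 to 100 for low back pain".

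For the other outcomes the same section names a test with no stratification: "For categorical outcome data, the chi-square test (or Fisher exact test) will be used". From section 2.10, the between-group comparisons concerned are whether any additional spondylolisthesis treatment was used, which types were used, early stopping versus completion of treatment, and adverse events. Section 2.13 assigns effectiveness to an intention-to-treat analysis and safety to a per-protocol analysis.

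**The concern.** The trial is stratified by institution in its design and adjusted for institution in its ANCOVA, but not in its categorical tests. The article gives no reason for the difference.

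The sites are two hospitals in two countries, with different kinds of practitioner delivering the Mokhuri treatment. After week 5, patients may seek other treatment as they wish. The rate of additional treatment could plausibly differ by site, and the Discussion itself names differences between the institutions as a potential problem.

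When the randomisation has balanced the arms within site, a pooled chi-square test still counts between-site variation as error. Its true type I error then lies below 5%, and it loses power. For adverse events, lower power makes a real difference in harm harder to see.

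**Working it through.** **Inputs.** From section 2.12: 108 and 14 participants. With 1:1 allocation within site this is 54+54 in Korea and 7+7 in the US. The significance level is 5%, taken as two-sided. The article gives no event rates, so all rates below are assumptions.

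**The plan's own figure.** 2 × (4.65 × (1.960 + 0.842) / 2.5)² = 54.31 per arm, and 54.31 / 0.9 = 60.3, rounded up to 61. The stated 61 per group reproduces. It concerns the pain score and does not depend on the categorical tests.

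**Why the pooled test is conservative.** Let w = 14/122 be the US share, so w(1−w) = (14 × 108)/122² = 0.1016. With balanced arms and no treatment effect, the pooled test uses p̄(1−p̄), which equals the within-site variance plus 0.1016 × (site gap)².
- Rates 30% Korea, 50% US: within-site variance 0.885 × 0.21 + 0.115 × 0.25 = 0.2146. The excess is 0.1016 × 0.04 = 0.0041, or about 2%.
- Rates 10% Korea, 90% US: within-site variance 0.09. The excess is 0.1016 × 0.64 = 0.065, or about 72%. The type I error is about 2Φ(−1.96 × √1.72) = 1.0%.

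**Check by enumerating all possible tables.** The pooled statistic is (x₁−x₀)²/61² divided by p̄(1−p̄) × 2/61. The CMH statistic is [Σ(x₁ₛ − mₛ/2)]² divided by Σ nₛ²mₛ(Nₛ−mₛ)/(Nₛ²(Nₛ−1)). Here nₛ is the number per arm at site s, Nₛ = 2nₛ, and mₛ is the number of events at that site. Neither uses a continuity correction.

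Type I error:

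| Korea / US rate | Pooled | CMH |
|---|---|---|
| 30% / 30% | 5.0% | 4.9% |
| 30% / 50% | 4.7% | 4.9% |
| 30% / 70% | 4.0% | 4.9% |
| 30% / 90% | 3.2% | 5.0% |
| 10% / 90% | 1.0% | 5.1% |

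Power:

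| Korea, two arms | US, two arms | Pooled | CMH |
|---|---|---|---|
| 30% vs 50% | 50% vs 70% | 62.8% | 62.9% |
| 20% vs 42% | 40% vs 62% | 73.9% | 74.6% |
| 15% vs 35% | 35% vs 55% | 71.5% | 71.8% |
| 30% vs 50% | 80% vs 95% | 60.6% | 61.7% |
| 20% vs 45% | 75% vs 95% | 81.9% | 85.1% |
| 20% vs 42% | 80% vs 95% | 69.7% | 75.1% |
| 15% vs 35% | 90% vs 98% | 60.1% | 71.0% |

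The first three rows have site gaps of 20 points and lose under 1 point of power. The last four have gaps of about 45 to 75 points and lose about 1, 3, 5 and 11 points.

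**Safety, per protocol.** Suppose exclusions leave 50+50 in Korea and 7+3 in the US, with adverse event rates of 10% and 80% and no treatment effect. The expected pooled rates are (5 + 5.6)/57 = 18.6% and (5 + 2.4)/53 = 14.0%, a spurious difference of 4.6 points. Type I error is 6.1% pooled and 4.8% with CMH. With 7+2 left in the US it is 9.9% against 4.9%. The retained numbers and the rates are illustrative.

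**The case against.** The strongest case against is that little depends on this. The primary outcome is continuous and its ANCOVA already includes institution. Only 14 of 122 participants are in the US stratum, so a visible loss of power needs very large site differences, and no document shows that these exist. While the arms stay balanced within site, the error is on the conservative side. All of this stands and keeps the point minor. It does not remove the mismatch, because the categorical test is stated text and not an omission.

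A reader might go further and infer that the repeated measures analysis also ignores site and baseline. The article says only: "To verify the trends for each visit in the 2 groups, repeated measures analysis of variance will be performed". It lists no model terms, so it neither includes nor excludes them, and a condensed article may leave such terms to a fuller plan. A constant shift between sites would also drop out of the group-by-visit test. Nor can a gain from baseline adjustment be counted here, since the planned ANCOVA already makes that adjustment.

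**Conclusion.** The plan is inconsistent for categorical outcomes: randomisation and ANCOVA use institution, while the chi-square or Fisher test does not. The consequence is small. Under the assumed rates, less than 1 point of power is lost for moderate site differences. The loss reaches about 5 to 11 points only in the scenarios where control-arm rates differ by 60 to 75 points.

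A reader might infer that the pooled tests produce too many false positives, or that the trial's main conclusion is at risk. Neither follows. With arms balanced within site the pooled test is conservative, and the primary analysis is already adjusted. The one qualification is the per-protocol safety comparison. If exclusions are uneven within site and adverse event rates differ strongly by site, the pooled test can be confounded and its type I error can exceed 5%. The article does not show that this will happen.

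**What to change.** In section 2.13, replace the chi-square or Fisher test for between-group categorical outcomes with a CMH test stratified by institution, in its exact form when counts are sparse. Report a site-stratified risk difference or odds ratio with it. Baseline tables can stay as they are.

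The cost is a change of wording. Institution is already recorded, and the sample size of 61 per group does not change. The only downside is that the 14-patient US stratum will need the exact form for rare events.
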